## Methods/Design

### Study design

The CDCS is a national, multicenter, non-interventional, 24 month prospective cohort survey in CKD patients on dialysis. The study includes a baseline visit and 4 other visits at 6 month intervals. The estimated enrollment period is 10 months. It is planned to consecutively recruit 1520 patients with ESRD receiving stable hemodialysis (HD) or peritoneal dialysis (PD) for at least 6 months in 24 dialysis centers in China. Participating centers will be selected based on logistics constraints. Consecutive patients who fulfill the inclusion and exclusion criteria and are willing to participate will be included in the study (Table 1). Written informed consents were obtained from all patients before participation. Each site is expected to enroll approximately 30 patients. After that, enrollment will be competitive at all sites. This study will be able to mirror real life management of these patients. All statistical analyses will be performed using SAS 9.2 software (SAS Institute, Cary, NC, USA). All hypothesis tests will use two-sided tests with a significance level of 0.05.

**Table 1 Tab1:** Inclusion and exclusion criteria of the CDCS

Inclusion criteria	Exclusion criteria
Male or female patients ≥18 years old	Patients’ life expectancy <6 months
Patients with ESRD receiving stable HD or PD for at least 6 months	Patients with acute kidney injury, active inflammatory diseases, parathyroidectomy or evident malignancies
Patient or legally accepted representative willing to sign Data Release Consent Form.	Patients with conditions making arterial calcification measurements technically impossible or unreliable, such as cardiac arrhythmias, amputations or severe peripheral vascular lesions
	Concomitant diseases that affect calcium status and soft tissue calcifications (sarcoidosis, multiple myeloma, HIV, amyloidosis)
	Pregnant or lactating women or women planning to become pregnant in the 6 months following entry into the study

*ESRD* End-stage renal disease, *HD* Hemodialysis, *PD* Peritoneal dialysis, *HIV* Human immunodeficiency virus

CKD is defined as abnormalities of kidney structure or function, present for >3 months, with implications for health, according to Kidney Disease: Improving Global Outcomes (KDIGO) 2012 Clinical Practice Guideline for the Evaluation and Management of CKD (Table 2) [19].

**Table 2 Tab2:** Criteria for CKD (either of the following present for >3 months)

	Criteria

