### Objectives

The primary objective for the CDCS is to determine the prevalence of VC in Chinese patients with CKD on HD or PD. The secondary objectives are:To test the hypothesis that a greater severity of baseline VC is associated with a higher risk for all-cause and CVD mortality, and non-fatal CV events in Chinese patients with CKD on HD or PD.To investigate the association between all-cause and CVD mortality, and non-fatal CV events and disease management (using serum levels of calcium, phosphorus and intact parathyroid hormone (iPTH), fibroblast growth factor 23 (FGF23) and related medications) in Chinese patients with CKD on HD or PD.To investigate the impact of current disease management on VC.To evaluate the control rate of patients achieving target goal of serum phosphorus, calcium and iPTH.To validate the cardiovascular calcification index (CCI) in Chinese patients with CKD on HD or PD.

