### Data collection

Visit 1 is at baseline/study entry and the follow-up includes 4 visits at 6 ± 1 month, 12 ± 1 month, 18 ± 1 months and 24 ± 1 month, respectively. The flow chart of detailed data and sample collection can be found in Table 3. At baseline, eligible patients will be evaluated for demographic information, smoking, alcohol drinking status, biochemical data, dialysis variables, concomitant medications, and personal and family disease history. Physical measurements including weight, height, body mass index (BMI) and vital signs (blood pressure and heart rate) will be obtained. Older age (male >55 years, female >65 years), arterial hypertension, family history (mother, father, brother, sister, children) of premature cardiovascular disease (≤55 years male, ≤65 years female), smoking, impaired glucose tolerance and/or impaired fasting glucose, dyslipidemia, and obesity are considered potent cardiovascular risk factors. The baseline biochemical data will be obtained using local routine laboratory methods performed within a week at the start of the study. If laboratory tests of serum 25-hydroxyvitamin D (25-OH Vit D) and FGF23 cannot be conducted in some centers, blood samples for testing 25-OH Vit D and FGF23 will be sent by the site study staff to those centers that can perform the assay. Blood sample collection will be performed according to the laboratory manual. Results from routine samples defined as samples taken within a week at the visit. Serum phosphorus, total calcium and iPTH will be tested at each visit. Target level of serum phosphorus, total calcium and iPTH in CKD stage 5 are defined according to Kidney Disease Outcomes Quality Initiative (K/DOQI) and KDIGO guidelines, respectively (Table 4) [20, 21]. Total serum calcium is adjusted if serum albumin is <4g/dL to better reflect the free calcium, using the formula proposed by the US Bone Metabolism Association: corrected total calcium (mg/dL) = total calcium (mg/dL) + 0.8 × [4.0 − serum albumin (g/dL)]. Date, time, primary reason and characteristics of death with autopsy results if applicable and any supportive documents that relate to fatal and nonfatal CV events are defined as clinical outcomes, and will be collected during the follow-up.

**Table 3 Tab3:** Study flow chart of the CDCS

Procedures	Visit time (month)				
	Baseline	6 ± 1	12 ± 1	18 ± 1	24 ± 1
Data release consent form	●				
Demography data	●				
Inclusion/exclusion criteria	●				

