### Secondary analysis

The key secondary analysis will be a comparison of survival (based on all-cause mortality) between patients with and without VC based upon the log-rank test performed at a significance level of 0.05. Hazard ratios and 95 % CIs will be calculated by a Cox proportional hazard regression model. In addition, the multivariable Cox proportional hazard regression model will be performed, using the stepwise method (*p* <0.05 as the inclusion criteria and *p* <0.10 as the exclusion criteria), considering with or without VC as the independent variable and the baseline variables with *p* <0.25 in univariate analysis as covariates, and hazard ratios and 95 % CIs for each factor will be presented. The same analyses will also be done for survival (based on CVD mortality) and non-fatal CV event free survival. For each of the above endpoints, the separate comparisons of patients with CAC, with AAC, with cardiac valve calcification to patients without VC will be made at a significance level of 0.05.

Association between disease management (including serum level of calcium, phosphorus and iPTH, and medications), 25-OH Vit D, FGF23, and all-cause/CVD mortality, non-fatal CV events will be identified with Cox proportional hazard regression model, considering disease management as the independent variables. Associations will be tested using the Wald test and described through the hazard ratios and 95 % CIs.

Association between disease management, 25-OH Vit D, FGF23, ankle-brachial index (ABI), and LVMI/LVH and the occurrence of CAC, AAC and cardiac valve calcification at baseline will be identified with the logistic regression model. The univariate logistic regression model will be performed separately, considering disease management, ABI, and LVMI/LVH as independent variables. Associations will be tested using the Wald test and described through the odds ratios and 95 % CIs.

Association between disease management, 25-OH Vit D, FGF23, ABI, and LVMI/LVH and severities (scores) of CAC, AAC and cardiac valve calcification at baseline will be identified with the linear regression model, considering disease management, ABI, and LVMI/LVH as independent variables.

Association between CAC progression and disease management, 25-OH Vit D, FGF23, ABI, as well as LVMI/LVH will be evaluated by ANCOVA as continuous variables and evaluated by ordinal multinomial logistic regression as categorical variables.

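### The key mortality test is an unadjusted log-rank in a non-randomised cohort, and the supporting Cox model chooses its confounders by p-value

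*Protocol article*

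**What the plan says.** Study design: "The CDCS is a national, multicenter, non-interventional, 24 month prospective cohort survey in CKD patients on dialysis". Under Objectives, the first secondary hypothesis is that "a greater severity of baseline VC is associated with a higher risk for all-cause and CVD mortality".

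Secondary analysis: "The key secondary analysis will be a comparison of survival (based on all-cause mortality) between patients with and without VC", tested by a log-rank at 0.05. No stratification factor or covariate is attached to that test. A multivariable Cox model is added, and "the multivariable Cox proportional hazard regression model will be performed, using the stepwise method", with entry at p<0.05 and removal at p<0.10. VC is named as the independent variable, and baseline variables with univariate p<0.25 come in "as covariates, and hazard ratios and 95 % CIs for each factor will be presented". No covariate is fixed in advance. The same analyses follow for cardiovascular death and for survival free of non-fatal cardiovascular events.

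For disease management and the occurrence of calcification at baseline: "The univariate logistic regression model will be performed separately, considering disease management, ABI, and LVMI/LVH as independent variables".

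Two other sections bear on confounding. Data collection lists older age, hypertension, smoking, glucose disorder, dyslipidemia and obesity among factors that "are considered potent cardiovascular risk factors". The CCI section awards points for age and dialysis vintage in the calcification index, which the plan then uses to predict coronary calcification. Determination of sample size rests on the log-rank test.

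**The concern.** On the document's own account, age is related both to having VC and to cardiovascular risk. Patients with and without VC are not randomised, so a log-rank test between them compares groups that probably differ in age, dialysis vintage and other prognostic factors. A significant key result could then appear although VC adds nothing to what those factors already predict.

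The added Cox model answers this only in part. Screening and stepwise rules keep a covariate because it is significant, not because it confounds. Weaker confounders can each miss the threshold and still bias the VC estimate together. The reported interval also takes the selected model as if it had been chosen beforehand.

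The univariate logistic models for disease management and VC occurrence have no confounder control at all. At stake are the mortality conclusion and the reading of the disease-management results.

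**Working it through.** **1. The plan's own figure.** Inputs (Determination of sample size): 2-year survival 0.79 with VC and 0.86 without, ratio 7:3, two-sided 0.05, 80 % power, 20 % loss.

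- HR, no VC versus VC = ln(0.86)/ln(0.79) = 0.6398; VC versus no VC = 1/0.6398 = 1.563.
- Freedman's log-rank formula, φ = 3/7: D = (1.960 + 0.842)² × (1 + φ·HR)² / [φ(1 − HR)²] = 229.2 deaths.
- Death probability = 0.7 × 0.21 + 0.3 × 0.14 = 0.189, so N = 229.2/0.189 = 1213, and 1213/0.8 = 1516.

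The stated 1520 is reproduced; it gives 1520 × 0.8 × 0.189 = 229.8 deaths and 80.1 % power. The sample size is right for the unadjusted test it was built for.

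**2. What age alone does to the crude test.** The documents give no age gap and no age hazard ratio, so both are assumptions. With no VC effect, crude HR ≈ (HR per decade)^(gap/10). The chance of significance is Φ(√(229.8 × 0.7 × 0.3) × ln HR − 1.96).

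| Age gap | 1.3 per decade | 1.5 per decade | 1.7 per decade |
|---|---|---|---|
| 5 years | 1.14 (15 %) | 1.22 (29 %) | 1.30 (45 %) |
| 8 years | 1.23 (31 %) | 1.38 (62 %) | 1.53 (84 %) |
| 10 years | 1.30 (45 %) | 1.50 (80 %) | 1.70 (96 %) |

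Simulation agrees. At 1.5 per decade and 8–10 years, the crude HR was 1.39–1.49, significant in 62–83 % of studies (150 per setting); a separate simulation at 10 years gave 1.47 and 71 %. Over the whole grid the simulated HR ran from 1.13 to 1.67.

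The gap needed to reach 1.563 is 10 × ln(1.563)/ln(HR per decade): 17.0, 11.0 or 8.4 years at 1.3, 1.5 or 1.7. Within the grid, only the top corner gets there.

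A binary confounder behaves likewise, with HR = [1 + p₁(RR − 1)]/[1 + p₀(RR − 1)], where p₁ and p₀ are its prevalence with and without VC. RR 2 at 60 % versus 20 % gives 1.6/1.2 = 1.33 (significant in 52 %). RR 1.5 at 40 % versus 20 % gives 1.2/1.1 = 1.09 (9 %).

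**3. What the stepwise model does.** Simulated with no VC effect, VC kept in the model, and the plan's 0.25, 0.05 and 0.10 rules:

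- Age the only confounder (150 runs): age was retained in 100 % of runs. False positives for VC were 6 %, the same as for the full model.
- Age plus six weak confounders, each 0.4 SD higher with VC. At HR 1.10 per SD (120 runs), 31 % of the weak ones were kept, VC HR 1.10, false positives 10 % against 4 % for the full prespecified model. At HR 1.15 per SD (60 runs), 58 % were kept, HR 1.08, 15 % against 5 %.
- Ten confounders at HR 1.10 per SD (400 runs): 3.1 of 10 were kept, HR 1.11, 95 % CI coverage 88 %. The full model gave 1.00 and 96 %.

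The run counts are small: the standard error is √(0.10 × 0.90/120) = 2.7 points for the 10 % and √(0.15 × 0.85/60) = 4.6 points for the 15 %. All the weak confounders act in one direction, which is unfavourable to stepwise selection.

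**4. Power of an adjusted test.** If VC has squared multiple correlation R² with the covariates (assumed), the effective deaths are 229.8 × (1 − R²). In Freedman's formula:

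| R² | Power at 1520 | N for 80 % |
|---|---|---|
| 0 | 80 % | 1516 |
| 0.1 | 76 % | 1684 |
| 0.2 | 71 % | 1895 |
| 0.3 | 65 % | 2166 |

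**The case against.** The plan does include adjustment, for all three outcomes, and a factor as strong as age would almost surely survive selection. The hypothesis is worded as association, which a crude comparison answers in part. The Discussion concedes the limits of an observational design. All of this stands, and it narrows the point, although that concession is general and does not mention confounding of VC by age.

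Four stronger readings go beyond the documents:

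- **Age alone explains the whole design effect.** This concerns only the crude test, and only near the top of the assumed range.
- **The adjusted HR is badly biased, with an interval shown to be too narrow.** The simulated bias is modest and comes from confounders stacked in one direction. Coverage of 88 % mixes that bias with interval width, so it does not isolate width.
- **VC itself passes through the stepwise procedure and is reported only when significant.** The text separates VC, as the independent variable, from the covariates. Its exemption from selection is not spelled out, but that is an ambiguity and not a stated rule.
- **All disease-management models are univariate.** The word is used only for the baseline logistic models. The Cox, linear, ANCOVA and ordinal models are not so described, and their covariates may be left to a fuller document.

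**Conclusion.** The point holds for the secondary objectives. The key mortality inference is a crude comparison in a non-randomised cohort, with confounders that the article itself names. Under assumed but moderate values (8–10 years, 1.5 per decade) it would often be significant with no VC effect, at an HR of about 1.4–1.5. Over 5–10 years and 1.3–1.7 per decade the HR is about 1.1–1.7.

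The stepwise model removes most of the age problem. What it leaves is smaller: a null HR of about 1.08–1.11 with several weak confounders, false positives of 10–15 % instead of 4–5 %, and intervals that ignore the selection. The univariate baseline logistic models are unadjusted as written. The prevalence estimates, which are the primary objective, are not touched, and the sample size is not in error for the log-rank test.

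**What to change.** In Secondary analysis:

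- Make the key mortality inference the VC hazard ratio from a Cox model with a covariate set fixed before outcomes are analysed and taken from baseline data already collected. Examples are age, sex, dialysis vintage, HD or PD, diabetes or glucose disorder, prior cardiovascular disease and smoking.
- State that VC always stays in the model, which also removes the ambiguity about selection.
- Delete the p<0.25 screen and the stepwise rule.
- Keep the log-rank test and Kaplan-Meier curves as description.
- Use the same set for the cardiovascular death and non-fatal event analyses, and add it to the baseline logistic models.

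About 230 deaths support such a list: with ten model terms, 229.8/10 is about 23 deaths per term.

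No new data are needed. The real cost is power, so Determination of sample size should state the power of the adjusted test: about 76 %, 71 % or 65 % at 1520 patients for an assumed R² of 0.1, 0.2 or 0.3, instead of 80 %. R² can be estimated from the baseline data, which the planned interim analysis examines, without looking at outcomes.

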Physical measurements (vital signs)	●				
Smoking and alcohol drink status	●				
Cardiovascular risk factors	●				
Disease history	●				
Concomitant medications	●	●	●	●	●
Hemoglobin, hematocrit	●				
Serum total calcium, phosphorus, iPTH	●	●	●	●	●
25-OH Vit D, FGF23	●		●		●
Glucose, HDL-C, LDL-C, TC and TG	●				
hs-CRP	●				
Serum albumin, ferritin, alkaline phosphatase	●				
Urea, uric acid, creatinine	●				
ABI	●				
Kt/V, dialysate calcium concentration	●				
Dialysis vintage, dialysis frequency and modality, membrane type	●				
EBCT or MDCT scan	●				●
Plain lateral lumbar radiograph	●				●
Echocardiography, LVMI/LVH	●				●
Clinical outcomes		●	●	●	●

*iPTH* Intact parathyroid hormone, *25-OH Vit D* serum 25-hydroxyvitamin D, *FGF23* Fibroblast growth factor 23, *HDL-C* High density lipoprotein-cholesterol, *LDL-C* Low density lipoprotein-cholesterol, *TC* Total Cholesterol, *TG* Triglyceride, *hs-CRP* High-sensitivity C-reactive protein, *ABI* Ankle-brachial index, *EBCT* Electron beam computed tomography, *MDCT* Multi-detector computed tomography, *LVMI* Left ventricular mass index, *LVH* Left ventricular hypertrophy

**Table 4 Tab4:** Target level of serum phosphorus, calcium and iPTH in CKD stage 5

Biochemical parameters	K/DOQI	KDIGO
Serum phosphorus	3.5–5.5 mg/dL (1.13–1.78 mmol/L)	Toward Normal [2.5–4.5 mg/dL (0.81–1.45 mmol/L)]
Corrected total calcium	8.4–9.5 mg/dL (2.10–2.38 mmol/L)	Maintain Normal [Healthy: 8.5–10.5 mg/dL (2.13–2.63 mmol/L)]
Serum iPTH	150–300 pg/mL (16.5–33.0 pmmol/L)	2–9 times the upper normal limit (65 pg/mL, 6.9 pmmol/L)

*K/DOQI* Kidney Disease Outcomes Quality Initiative, *KDGIO* Kidney Disease: Improving Global Outcomes, *iPTH* Intact parathyroid hormone

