### Imaging methods

VC images will be taken within a week of enrolment and the final visit of the study. Coronary artery calcification (CAC), abdominal aortic calcification (AAC) and cardiac valve calcification will be assessed by electron beam computed tomography (EBCT) or multi-detector computed tomography (MDCT), plain lateral lumbar radiograph and echocardiography, respectively. In addition, results of left ventricular mass index (LVMI) and left ventricular hypertrophy (LVH) through echocardiography will be taken within a week of enrolment and the final visit of the study as well.

CAC is measured by EBCT or MDCT as originally described by Agatston et al. [22]. Thirty to forty contiguous tomographic slices will be obtained at 3-mm intervals beginning 1 cm below the carina and progressing caudally to include the entire coronary tree. An attenuation threshold of 130 Hounsfield units (HU) and a minimum of 3 contiguous pixels will be used for identification of a calcific lesion. The density factor is assigned in the following manner: 1 for lesions with peak attenuation of 130–199 HU, 2 for lesions with peak attenuation of 200–299 HU, 3 for lesions with peak attenuation of 300–399 HU, and 4 for lesions with peak attenuation >400 HU [22]. Total CACS is determined by summing individual lesion scores from each of four anatomic sites (left main, left anterior descending, left circumflex, and right coronary artery). The CACS will be divided into approximate tertiles (0, <100, ≥100, ≥400 and ≥1000). CAC progression is evaluated as a continuous variable by calculating the difference in Agatston score between the two CT scans divided by the time between imaging. The 2-year progression of CAC is categorized as follows: absent (≤25th percentile), moderate (25th-75th percentiles), and accelerated (≥75th percentile).

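### Baseline presence of calcification is related to disease management by univariate models only, leaving age and dialysis vintage uncontrolled, and the only stated longitudinal analysis of calcification is for CAC

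*Protocol article*

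**What the plan says.** The Objectives section of the protocol article lists, among the secondary objectives, "To investigate the impact of current disease management on VC". It refers to VC as a whole and names no site.

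The Secondary analysis section relates disease management to calcification in three ways:

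- **Presence.** Association with "the occurrence of CAC, AAC and cardiac valve calcification at baseline will be identified with the logistic regression model". The only form described is: "The univariate logistic regression model will be performed separately, considering disease management, ABI, and LVMI/LVH as independent variables".
- **Severity.** Association with "severities (scores) of CAC, AAC and cardiac valve calcification at baseline will be identified with the linear regression model". The text does not say whether this model has one factor or several.
- **Progression.** ANCOVA and ordinal logistic regression, for CAC only. The Imaging methods section likewise defines a change measure for the Agatston score but none for the AAC score or the valves.

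On timing, "The baseline biochemical data will be obtained using local routine laboratory methods performed within a week at the start of the study". Also, "VC images will be taken within a week of enrolment and the final visit of the study". Table 3 marks the CT scan, the lumbar radiograph and the echocardiogram at baseline and month 24. It marks calcium, phosphorus, iPTH and medications at all five visits.

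**The concern.** The objective asks about the impact of management. The presence models set one week's laboratory values and current medication against calcification that is already there, in patients with at least six months of dialysis behind them. Values measured at entry do not precede that calcification, and known calcification may itself influence which drugs a patient receives.

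The models as described also contain no confounders. Age and dialysis vintage are plausible common correlates of mineral values, medication and calcification, and the protocol treats both as markers of calcification. A crude odds ratio for phosphorus, calcium, iPTH or a drug therefore mixes its own association with theirs.

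At stake is the reading of one secondary objective. An unadjusted baseline association could be reported as an effect of management, or a real association could be missed. Data that place exposure before outcome are already scheduled at all three sites, but a progression analysis is stated for only one.

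**Working it through.** **1. Objective, data and analysis by site**

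| Site | Imaging at baseline and month 24 | Stated baseline presence model | Stated severity model | Stated progression analysis |
|---|---|---|---|---|
| CAC | EBCT or MDCT | Univariate logistic | Linear, adjustment not stated | ANCOVA, ordinal logistic |
| AAC | Lateral lumbar radiograph | Univariate logistic | Linear, adjustment not stated | None stated |
| Valves | Echocardiogram | Univariate logistic | Linear, adjustment not stated | None stated |

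The univariate form applies to all three sites. What sets AAC and valves apart is only the last column.

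**2. Whether age and vintage matter by the protocol's own account**

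The CCI gives up to 2 points for age, 1 for vintage, 3 for the aortic valve, 1 for the mitral valve and 4 for the abdominal aorta: 2 + 1 + 3 + 1 + 4 = 11, the stated maximum. Age and vintage supply 3 of the 11. Table 3 collects demography and dialysis vintage at baseline, so adjustment needs no new data. The same section specifies a multivariable Cox model for mortality. Describing only a univariate model for presence is thus a stated choice.

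**3. How far a crude odds ratio can move (illustration)**

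Assumptions, none of them from the document except the first: presence in 70 % (the 7:3 ratio in the sample-size section, which is for any VC and not for a single site); true phosphorus odds ratio 1.20 per SD; age odds ratio 2.0 or 2.5 per SD; age and phosphorus standard normal with correlation r.

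To first order, crude log OR ≈ ln(1.20) + r × ln(age OR).

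- r = -0.2, age OR 2.0: 0.182 - 0.2 × 0.693 = 0.044, OR about 1.04.
- r = -0.2, age OR 2.5: 0.182 - 0.2 × 0.916 = -0.001, OR about 1.00.

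The exact crude odds ratio, by numerical integration of the logistic model:

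| r | Crude phosphorus OR (age OR 2.0 and 2.5) |
|---|---|
| -0.3 | 0.98 and 0.92 |
| -0.2 | 1.04 and 1.00 |
| -0.1 | 1.11 and 1.08 |
| 0 | 1.18 and 1.17 |
| +0.1 | 1.26 and 1.27 |
| +0.2 | 1.34 and 1.37 |
| +0.3 | 1.43 and 1.49 |

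The small drop from 1.20 at r = 0 is non-collapsibility of the odds ratio. The rest is confounding. Negative correlation hides or reverses the association, and positive correlation inflates it.

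**4. How many patients would have paired images**

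Inputs from the sample-size section: 1520 patients, 20 % two-year mortality, 20 % loss, and survival of 0.79 and 0.86 in groups of 1064 and 456.

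- 1520 × 0.80 × 0.80 = 973.
- (1064 × 0.79 + 456 × 0.86) × 0.80 = 1232.7 × 0.80 = 986.

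Roughly 970 to 990 patients would be alive and retained at month 24, before any allowance for missed or unreadable images.

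**The case against.** **The article is condensed.** A full protocol or analysis plan may exist, and a progression model for AAC or valves could be in it. This stands. A reader might infer that no such analysis is planned at all, or that the study cannot address impact at two of its three sites. An article's silence does not support that. The firm part of the point is what the article does state: presence models fixed to baseline and described as univariate.

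**CAC progression is a defensible choice.** The objective does not promise an answer for each site, and the Agatston score is continuous, whereas AAC is a 0 to 24 grading and valves form three groups. This also stands, which is why the added analysis is proposed as supporting only.

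**The section speaks of associations.** Its paragraphs claim association and label the models as baseline. The word impact comes from the objective and the abstract. So the reporting fix asks for consistency and does not correct a causal claim in the analysis section.

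**The month-24 echocardiogram may be used.** A reader might infer that the second examination serves no analysis. It also yields LVMI and LVH, which enter the CAC progression model at an unstated visit. Only the repeat radiograph and the repeat valve reading lack a stated analysis.

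**The univariate wording is limited.** It covers CAC presence as well as AAC and valves, and it is not applied to the linear severity models. It cannot be presented as a defect of two sites or of every baseline model.

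**The magnitude is hypothetical.** A reader might infer that a real phosphorus effect would vanish or reverse. That follows only from negative correlations of sufficient size. Positive ones exaggerate the effect, and the document gives none.

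**Conclusion.** The point holds in a limited form. For the objective on management and VC, the stated presence models are cross-sectional and unadjusted at all three sites. They omit age and dialysis vintage, which the study collects and which its own index scores. Their odds ratios can be biased in either direction. The 0.92 to 1.49 range around a true 1.20 shows what the assumed inputs imply and is not an estimate for this cohort.

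Secondly, CAC progression is the only longitudinal analysis of calcification stated, although radiograph and valve images are repeated at month 24. This part is weaker because an unseen document may fill it.

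The consequence is confined to one secondary objective. Baseline prevalence, the primary analysis, and survival by VC status, the key secondary analysis, are not touched. The change is worth making because it is cheap and improves the answer to that objective.

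**What to change.** 1. Make the baseline presence models multivariable, adjusted for age, sex, dialysis vintage, diabetes and dialysis modality. Use the same covariates in the linear severity models if they are not already adjusted.
2. Add a supporting analysis of data already scheduled: 24-month change in AAC score, and new or additional calcified valves, modelled on time-averaged phosphorus, calcium, iPTH and medication from baseline to month 18, adjusted for baseline score and the covariates above. If the full protocol or analysis plan already contains this, refer to it.
3. Base any statement of impact on the progression models, and report the baseline models as cross-sectional associations.

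The cost is plan wording and programming, with no new visits, images or assays. The progression analyses are limited to survivors with repeat images (roughly 970 to 990 on the protocol's own rates), so they describe a selected group and should be reported as such.
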